## Abstract

**Background:**

Treatment-resistant depression (TRD) is the inability of a patient with major depressive disorder (MDD) to accomplish or achieve remission after an adequate trial of antidepressant treatments. Several combinations and augmentation treatment strategies for TRD exist, including the use of repetitive transcranial magnetic stimulation (rTMS), and new therapeutic options are being introduced. Text4Support, a text message–based form of cognitive behavioral therapy that allows patients with MDD to receive daily supportive text messages for correcting or altering negative thought patterns through positive reinforcement, may be a useful augmentation treatment strategy for patients with TRD. It is however currently unknown if adding the Text4Support intervention will enhance the response of patients with TRD to rTMS treatment.

**Objective:**

This study aims to assess the initial comparative clinical effectiveness of rTMS with and without the Text4Support program as an innovative patient-centered intervention for the management of patients diagnosed with TRD.

**Methods:**

This study is a multicenter, prospective, parallel-design, 2-arm, rater-blinded randomized controlled pilot trial. The recruitment process is scheduled to last 12 months. It will involve active treatment for 6 weeks, observation, and a follow-up period of 6 months for participants in the study arms. In total, 200 participants diagnosed with TRD at rTMS care clinics in Edmonton, Alberta, and rTMS clinics in Halifax, Nova Scotia will be randomized to 1 of 2 treatment arms (rTMS sessions alone or rTMS sessions plus Text4Support intervention). Participants in each group will be made to complete evaluation measures at baseline, and 1, 3, and 6 months. The primary outcome measure will be the mean change in the scores of the Patient Health Questionnaire-9 (PHQ-9). The secondary outcome measures will involve the scores of the 7-item Generalized Anxiety Disorders Scale (GAD-7), Columbia-Suicide Severity Rating Scale (CSSRS), and World Health Organization-Five Well-Being Index (WHO-5). Patient data will be analyzed with descriptive statistics, repeated measures, and correlational analyses. Qualitative data will be analyzed using the thematic analysis framework.

**Results:**

The results of the study are expected to be available 18 months from the start of recruitment. We hypothesize that participants enrolled in the rTMS plus Text4Support intervention treatment arm of the study will achieve superior outcomes compared with the outcomes of participants enrolled in the rTMS alone arm.

**Conclusions:**

The application of the combination of rTMS and Text4Support has not been investigated previously. Therefore, we hope that this study will provide a concrete base of data to evaluate the practical application and efficacy of using the novel combination of these 2 treatment modalities.

**International Registered Report Identifier (IRRID):**

PRR1-10.2196/46830

## Introduction

### Background

Major depressive disorder (MDD) is one of the most prevailing mental health conditions, which affects about 300 million people globally [1]. MDD is considered the second leading cause of years lived with disability, and it was associated with an estimated worldwide loss of over 63 million healthy years in 2010 [2,3]. The lifetime prevalence of MDD stands at 15% [4], with a substantial socioeconomic impact and an estimated annual cost of about US $236 billion and €91 billion (US $96 billion) in the United States and Europe, respectively [5,6]. The lifetime prevalence of MDD within the Canadian population stands at 9.9% [7], with an estimated annual economic cost of about US $12 billion [8]. Data demonstrate that among MDD patients who receive first-line treatment, about 50% fail to achieve remission, with two-thirds requiring further treatment trials before they can reach the state of remission [9,10].

Most MDD patients may respond to treatment modalities, which include conventional psychopharmacology, psychotherapy, and electroconvulsive therapy. However, about one-third of patients fail to respond to these treatment modalities and hence are diagnosed with treatment-resistant depression (TRD) [11,12]. Owing to the heterogeneity of MDD and the absence of clear biological predictors of what constitutes a response to a specific treatment agent, there is a high chance of any patient with treatment failure being classified as treatment resistant [13,14].

The concept of TRD spans over decades [15]. While many definitions of TRD have been proposed in the literature, the consensus appears to center on the failure of an MDD patient to respond to 2 adequate trials of recommended antidepressant pharmacotherapy [16]. However, the term “adequate response” may be in contention regarding the precise meaning of what constitutes “adequate.” Generally, it has been argued that “TRD” may not be the best term to describe the nonresponse to therapeutic modalities in patients with MDD [16]. Instead, the term “difficult-to-treat depression” has been proposed in the literature. It has the added benefit of preventing MDD patients from feeling that their condition is impossible to treat with the recommended treatment modalities [17]. In Canada, TRD is diagnosed based on nonresponse to at least two antidepressant medications from different classes [18].

Data in the literature suggest that TRD is characterized by a disproportional socioeconomic burden for affected individuals, their relatives, and the health care system in general [19]. TRD presents with a higher direct and indirect medical cost than MDD, which is responsive to therapeutic interventions. This medical cost increases with the severity of TRD [20-23]. Compared with other depressive conditions, TRD leads to at least about 12% more outpatient attendance, is associated with about twice the chances of hospitalization, and is associated with the use of up to about 3 times more psychopharmacological medications [22]. Evidence in the literature suggests that the overall medical cost for hospitalization among patients with TRD is about 6 times greater compared to that among patients without TRD [22]. Similarly, the total cost of a TRD episode among patients with TRD is about 2.7 to 5.8 times higher compared to that among patients without TRD. This difference in cost is due to a longer duration of TRD episodes coupled with a greater rate of usage and a higher cost per treatment visit among patients with TRD [23]. Furthermore, the overall depression-related cost among patients with TRD is estimated to be about 19 times greater compared to that among patients with other depressive conditions [22]. Data suggest that up to about 47% of depression-related costs are attributed to TRD in the United States alone [21,24].

TRD is associated with several risk factors, which include physical or psychiatric conditions, such as anxiety disorders, personality disorders, and hypothyroidism; drug interactions; sociodemographic risk factors, such as individual education attainment and gender; and other external issues affecting ill health [21,25-27]. Furthermore, bipolarity is considered a major factor in TRD based on the inadequate management of bipolar diathesis in MDD, which is diagnosed as unipolar [26,28,29]. Again, TRD is characterized by a greater risk of comorbidities of both psychiatric and medical conditions, an increased risk of suicides, and impairment in normal functioning such as impaired quality of life and social functioning [20,30-32]. Due to its recurrent nature, an estimated 80% of patients with TRD relapse within 1 year after remission of their symptoms [30].

The prevalence of TRD varies significantly across the literature (12%-55%) [21,33-35]. In the United States alone, the estimated annual prevalence of medication-treated MDD was 8.9 million adults, of which 2.8 million (30.9%) had TRD [24]. A study that evaluated the prevalence and burden of TRD among patients with MDD in 4 Latin American countries (Argentina, Mexico, Colombia, and Brazil) revealed that 29% of the study participants with MDD were resistant to medication. The results demonstrated a TRD prevalence of 33% in Argentina, 21% in Mexico, 32% in Colombia, and 40% in Brazil [19]. In Europe, data from a multicenter study of patients with TRD suggested a prevalence rate of 41% among patients with MDD, while in the United Kingdom, a study conducted on patients treated for MDD in a primary care setting demonstrated that 55% of the patients had TRD [36,37]. In Canada, the prevalence of TRD is about 21.7%. However, there were no differences in prevalence between men and women or among ethnic groups [18]. The wide variation in prevalence estimates is not unconnected with the variation in the definition and criteria for classifying TRD in the literature.

### Treatment Options for TRD

Since the idea of TRD was established in 1974 [38,39], there has not been any straightforward standardized technique made available for the management of TRD; however, several studies have been conducted to evaluate the optimum treatment modalities for the same [40,41]. Many different psychopharmacological and nonpharmacological agents have been proposed and considered for the management of TRD. These treatment strategies may consist of psychopharmacological options, such as switching, augmentation, combination, and optimization of antidepressant medications [42]. Other comprehensive strategies include electroconvulsive therapy [43], psychotherapy [44], exercise [45], deep brain stimulation [43], light-based therapy [45], yoga [45], and transcranial magnetic stimulation (TMS) [43].

### Use of Repetitive TMS in the Treatment of TRD

TMS was developed in the late 1980s [46]. Subsequently, researchers came up with newer techniques to deliver multiple pulses of TMS in shorter intervals referred to as repetitive TMS (rTMS) [47]. Thereafter, several studies were conducted to evaluate the efficacy of rTMS for the management of MDD [48] and other psychiatric conditions. rTMS is effective in the management of TRD, with response rates ranging from 30.6% to 64.7% [49-54]. In 2002, the application of rTMS for the management of TRD was approved by Health Canada [16].

rTMS is a noninvasive brain stimulation treatment modality that is deemed to be a valuable and promising treatment technique for TRD [55]. Two main protocols of rTMS are mostly used in the management of TRD: low-frequency (≤1 Hz) rTMS targeting the right dorsolateral prefrontal cortex and high-frequency (5-20 Hz) rTMS targeting the left dorsolateral prefrontal cortex [56]. Studies have argued that there is no significant difference in the efficacy of low-frequency rTMS and high-frequency rTMS in the management of patients with MDD. However, high-frequency rTMS seems better suited in clinical practice owing to the placebo effect [57,58]. The rTMS protocol of choice commonly used in suicide interventions (a common feature of TRD) is high-frequency rTMS [59,60]. The evidence in the literature in support of rTMS as a suicide reduction treatment intervention is modest and yet promising. Although there have been variations in the rTMS protocol among studies, several studies have demonstrated reductions in the rates of suicidality, with remission rates ranging from 40% to 65% in patients diagnosed with depressive disorders [59-63].

A standard session of rTMS for the management of TRD may consist of 20 to 30 daily treatment sessions for 4 to 6 weeks [64]. The administration of rTMS does not require an anesthetic agent and hospitalization, and thus, it is more accessible compared to electroconvulsive therapy in the management of TRD. Furthermore, rTMS application is deemed safe and tolerable, with no serious adverse effects among users [65].

### Digital Technology Used in the Treatment of TRD

Though many treatment interventions for depressive conditions have been proposed in the literature, it is quite obvious that the traditional face-to-face means of delivering mental health care alone will not be enough to meet the demands for health care services, given the high prevalence of MDD and TRD, without any hope or likelihood of a decrease any time soon [66]. According to the 2012 Canadian Community Health Survey on Mental Health, about 2.3 million Canadians mentioned among other things that the barriers hindering them from accessing quality mental health care include a lack of a readily available care system, stigma, and high cost of health care services [67,68]. There has been a significant advancement in the development of digital technologies for the provision of health care in recent decades [69]. In particular, mobile digital information and communication technologies continue to advance at an exponential rate, making it possible to communicate, obtain information, and access care services with ease.

There is evidence in the literature in support of the therapeutic efficacy and cost-effectiveness of these digital technologies, such as tele-mental and e-mental health services, with the potential of enhancing easy access to health care and thereby helping to reduce the decades-old problem of unmet treatment needs and the wide treatment gap for mental conditions, particularly TRD [70,71]. These useful technological methods of health care delivery include smartphone apps, text messages, and email messaging [71,72]. In 2019 alone, about 97% of the world’s population lived in communities with coverage of mobile cellular signals [73]. This exponential growth of mobile networks and phones has greatly opened new opportunities for health care delivery and health promotion, with a significant improvement in mobile health within recent years [74]. A global survey conducted in 2015 demonstrated that Canada, among Western countries, is in the high internet use group, with about 90% of Canadians using internet services and 67% owning a smartphone [75]. In 2022, internet usage among individuals aged 15 years or above in Canada increased to 95% from 92% in 2020. Notably, there was a significant rise in usage among those aged 75 years or older, with an increase from 62% in 2020 to 72% in 2022 [76].

Technology-enabled cognitive behavioral therapy–based programs have been increasingly acknowledged as innovative, accessible, cost-effective, and acceptable ways of delivering psychological treatments to patients and the general public with mental health problems [77]. An estimated 99% of all messages received on mobile phones are opened, and about 90% of all text messages end up being read within 1 to 3 minutes of reception [78]. Thus, providing an affordable means of accessing care could help close the psychological treatment gap for patients with TRD [79].

Text4Support is one of the supportive text messaging programs in the ResilienceNHope [80] suite delivered by the Global Psychological eHealth Foundation [81]. The program allows users to receive daily supportive text messages, which have been written by a team of cognitive behavioral therapists and mental health professionals in collaboration with users of mental health services. The aim of this Text4Support depression program is to positively enhance the mood of patients with clinical depression. The program operates using positive reinforcement to correct distorted or negative thought patterns.

Evidence in support of the therapeutic efficacy of supportive text messaging exists from randomized controlled trials (RCTs) on supportive text messaging for the management of MDD conducted in Canada [82] and Ireland [83]. In these trials, patients with MDD were offered twice daily supportive text messages in addition to their usual care. Overall, there were significantly greater reductions in the symptoms of MDD among patients in the intervention group than among those in the control group receiving only usual care. After 3 months, the study in Canada demonstrated a statistically significant difference in the mean Beck Depression Inventory-II (BDI-II) score between the intervention group and the control group (mean change of −7.6, 95% CI −13.2 to −1.9; Cohen *d*=0.67) in favor of the intervention group [82]. Similarly, the RCT conducted in Ireland demonstrated a statistically significant difference in the BDI-II score between the intervention group and the treatment as usual group (mean change of −7.9, 95% CI −13.06 to −2.76; Cohen *d*=0.85) in favor of the intervention group [83]. User satisfaction with the Text4Support intervention and related programs has been assessed and reported in several other studies [79,84]. About 83% of users of the Text4Mood program reported an overall improvement in their mental health conditions, which they attributed to receiving daily supportive messages [79].

This study seeks to investigate the combined effect of an rTMS intervention with and without a text message–based cognitive behavioral therapy program (Text4Support) in patients diagnosed with TRD. The study also aims to generate effect size data for these interventions, which will help inform sample size and power calculations for a full-scale randomized clinical trial.

## Methods

### Study Design and Setting

This study is a multicenter, prospective, parallel design, 2-arm, rater-blinded randomized controlled pilot trial. Participants will be randomly assigned to 1 of 2 treatment conditions. The first condition includes rTMS sessions combined with Text4Support. The second condition includes treatment as usual (rTMS sessions alone). The recruitment process is scheduled to last 12 months. It will involve active treatment for 6 weeks and follow-up with observation periods of 6 weeks, and 3 and 6 months for participants in both arms of the study. Figure 1 presents the CONSORT (Consolidated Standards of Reporting Trials) flowchart for the project. Participants will be recruited from 4 different centers for this project. Two centers (the Addiction and Mental Health Clinic and the Alberta Day Hospital) are from the large sociodemographically diverse city of Edmonton in Alberta, Western Canada. The remaining 2 centers are in Halifax and Annapolis Valley in Nova Scotia, Canada. Table 1 presents the proposed timelines for this project.

**Figure 1 figure1:**
[figure not shown]
CONSORT (Consolidated Standards of Reporting Trials) flowchart. AHS: Alberta Health Services; rTMS: repetitive transcranial magnetic stimulation.

**Table 1 table1:** Gantt chart displaying project timelines.

Milestone		Year 1					Year 2	
		Q1	Q2	Q3	Q4	Q1		Q2
**Milestone 1: Recruitment and training of trainees in psychiatry, and setting up of infrastructure for the delivery of Text4Support**								
	1.1. Advertising and recruitment of a trainee in psychiatry who will support the research/evaluation of the project component, apply rTMS^a^, and facilitate the delivery of Text4Support	✓						
**Milestone 2: Recruitment of study participants**								
	2.1. Recruitment, baseline assessment, and randomization		✓	✓				
	2.2. Assignment into 1 of the 2 arms of the study		✓	✓				
	2.3. Delivery of Text4Support and rTMS to participants		✓	✓	✓			
**Milestone 3: Follow-up assessment of study participants**								
	3.1. Follow-up assessment of individual study participants				✓	✓		
	3.2. Follow-up satisfaction survey of participants in all groups				✓	✓		
**Milestone 4: Data compilation, data analysis, and preparation of reports, publications, and presentations**								
	4.1. Data compilation		✓	✓	✓	✓		✓
	4.2. Data analysis		✓	✓	✓	✓		✓
	4.3. Preparation of reports, publications, and presentations							✓

^a^rTMS: repetitive transcranial magnetic stimulation.

### Participants

We aim to randomize 200 patients (Edmonton/AB=120 and Halifax/NS=80) in this study.

#### Inclusion Criteria

The inclusion criteria are as follows: (1) Age 18 years or above; (2) Diagnosis of MDD based on the Diagnostic and Statistical Manual of Mental Disorders, Fifth Edition criteria, and failure of at least two standard antidepressant treatments during the current episode; (3) Good understanding of the English language; (4) Possession of a smartphone, and ability to receive and read text messages; and (5) Ability to consent, and willingness to provide written informed consent.

#### Exclusion Criteria

The exclusion criteria are as follows: (1) Age less than 18 years; (2) Diagnosis (current unless otherwise stated) of a neurological disorder (including a history of seizures), a primary or secondary tumor in the central nervous system, cerebrovascular disease, stroke, cerebral aneurysm, or movement disorder; (3) Diagnosis of a current psychotic disorder, such as substance-induced psychosis, psychotic disorder due to a medical condition, or MDD with psychotic features at the time of screening; (4) Diagnosis of a current personality disorder that may hinder participation in this research or may have the potential of affecting cognition and the ability to fully participate in the study; (5) Presence of a learning disability as identified through medical history or by the investigator during the assessment process; (6) Involvement in any drug or device clinical trial within the last 6 weeks before the screening visit or involvement in another clinical trial for the duration of this study; and (7) Identification of or the sudden appearance of any condition identified by the investigators to have the potential to hinder the progress and completion of the trial, or be a confounding factor for the outcome assessment.

### Sample Size Calculation

This study is a pilot study with no standardized data documented on the effect size, which could aid in power and sample size calculations. We will therefore use data that can be generated from the study participants recruited within the existing protocol. This approach is accepted for pilot studies that consist of novel interventions, such as this, and this method has been described by Haynes et al [85] as using “the participants I can get.” In this regard, the study will be limited to a sample size of about 200 (120 from Edmonton and 80 from Halifax), with 100 participants recruited in each of the study arms. Since TRD is characterized by periods of relapses and depressive attacks, we anticipate a certain number of eligible patients to decline to enroll in the study or even drop out before the completion of the study.

### Recruitment Process

Participant eligibility will be determined by the rTMS specialist team within the various centers. If found eligible for inclusion in the rTMS program, the patient will be approached by a member of the study team to introduce the study. A copy of the information leaflet will be provided to patients to have a detailed insight into the study processes. Once the patients agree to take part in the study, they will be asked to sign a consent form. The signing of the consent form and recruitment process will be conducted face-to-face at the various study sites during the week of the rTMS eligibility assessment of the participants, which usually occurs 1 week before the rTMS sessions begin. Participation in the study is by choice, and a participant can decide to withdraw at any time without providing a reason. To withdraw from the study, participants can contact the research coordinator to communicate their decision to discontinue their participation in the study. Once withdrawn, the study will not collect any new information about them, and if deemed fit, the said participants may approach the research team to withdraw all data collected on them before the study data are analyzed or disseminated.

### Randomization and Blinding

A simple randomization technique will be employed using a single sequence of random assignments. The simple randomization will be performed using a computer-generated Excel sheet (Microsoft Corp). To ensure balance (1:1), the randomization will be stratified by using permuted blocks. The codes generated will then be transmitted via text message by an independent statistician directly to a blinded researcher’s password-protected phone line with a secure online backup. This process will occur for enrollment as each participant signs the consent form.

Since blinding of participants in this study is impossible, their treatment allocation will be made known to them right after the randomization process. Primary outcome assessors will not be granted access to the database that contains the randomization codes, and they will not be involved with all discussions concerning the study participants and may be blinded to the treatment arm allocations. The data that would be generated from the study will undergo a blind review for the reason of finishing the planned analysis.

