Additionally, participants in the rTMS plus Text4Support group of the study will be assisted by a study team member to register into the Text4Support program. The process will require all participants in this arm of the study to input their phone numbers into the Text4Support platform, which will be used to deliver daily messages. Starting a day after enrollment, participants will receive daily supportive text messages designed by mental health therapists, clinical psychologists, psychiatrists, and mental health service users. These messages will be based on cognitive behavior therapy principles crafted to positively enhance the mood of users with depressive symptoms and other related mental health problems of concern. The messages will be preprogrammed into a software program that will deliver the messages automatically to the participants’ mobile phones at 10 AM (Mountain Time) and 12 PM (Atlantic Time), and each participant will receive these messages continuously for 6 weeks.

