### Data Collection and Follow-Up Assessment

All study participants who provide informed written consent and agree to participate in the study will be asked to complete a baseline assessment questionnaire that captures both demographic and clinical information. Study participants will also be asked to complete various follow-up assessments related to primary and secondary outcome measures at 6 weeks, and 3 and 6 months from enrollment. All self-completed surveys will be completed online on tablets or on participants’ cell phones. Clinician-rated scales will be completed either face-to-face at the study sites or over the phone/video conference with the help of a blinded researcher. All follow-up survey links will be delivered to participants’ cell phones at the designated time points. Two reminder text messages will be sent a day apart to encourage participants to complete the follow-up surveys. Participants who do not complete the online surveys despite receipt of 2 reminder text messages will be contacted by a research team member to ascertain if there are any barriers to survey completion and if any assistance is needed. Qualitative data collection will be in the form of a patient experience questionnaire and a key informant interview via telephone, which will be conducted at 3 and 6 months. Data related to participants’ clinic or program attendance rates and use of health services will be compiled from administrative records by a blinded researcher at 6 months.

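### Randomisation codes go to a researcher labelled blinded, assessors only may be blinded, and the one clinician-rated scale (CSSRS) is not clearly covered by any blinding safeguard

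*Protocol article*

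**What the plan says.** Randomization and Blinding describes the handling of codes in three steps. On transmission: "The codes generated will then be transmitted via text message by an independent statistician directly to a blinded" researcher, whose phone line is the stated destination. On timing: "This process will occur for enrollment as each participant signs the consent form". Participants are not blinded: "their treatment allocation will be made known to them right after the randomization process".

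The same section then turns to assessors. Those who assess the primary outcome are denied the database holding the codes. Of them it adds: "they will not be involved with all discussions concerning the study participants and may be blinded to the treatment arm allocations".

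Data Collection and Follow-Up Assessment uses the blinded-researcher label twice more. On ratings: "Clinician-rated scales will be completed either face-to-face at the study sites or over the phone/video conference with the help of a blinded researcher". It also has a blinded researcher compile attendance and service-use data from administrative records at 6 months.

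Table 2 gives the client as rater of the PHQ-9, GAD-7 and WHO-5, and the clinician as rater of the CSSRS. The Abstract and Study Design and Setting call the trial rater-blinded. Strengths of This Study says that all primary outcome assessors are blinded and that this removes rater bias.

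**The concern.** Three things do not fit together.

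- The person who receives each allocation as it is made is called blinded.
- The same label is then used for the people whose blinding is meant to protect the staff-rated scale and the administrative data.
- The sentence that should fix assessor blinding is permissive, while the design label and the stated strength treat it as settled.

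What is at stake is the meaning of rater-blinded in this trial. Rater blinding can operate only where a member of staff makes the rating. Among the listed outcome measures that is the CSSRS alone, a suicidality measure reported as a risk category. If its rater knows the arm, the one protection that the design label promises is lost. If the claim under Strengths of This Study is carried into the trial report, readers will credit the primary outcome with a protection it does not have.

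**Working it through.** No arithmetic applies. The sample size is one of convenience and this point depends on no power input. The check sets the statements side by side.

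**1. Can the code recipient be blinded?** The codes arrive one participant at a time, at consent, and each participant learns the arm straight afterwards. The only site-side recipient named is the blinded researcher. If the code shows the arm, the recipient knows every allocation received. If blinded means only that the recipient does not know upcoming allocations, that is allocation concealment; it says nothing about allocations already made. If the code is unreadable to the recipient, someone else must decode it, and the article names no such person.

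**2. Are the roles kept apart?** The label occurs once for receiving codes, once for helping with clinician-rated scales and once for compiling administrative data. No sentence says that these are different people, and none says that they are the same. A site could give all three tasks to one person and still comply with the text.

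**3. Is assessor blinding fixed?** Randomization and Blinding says "and may be blinded to the treatment arm allocations". The Abstract, Study Design and Setting, and Strengths of This Study all present rater blinding as a fact. The methods sentence is weaker than the three statements that rest on it.

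**4. Whom does the access bar protect?** It names primary outcome assessors. The table sets this against Table 2.

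| Scale | Status | Rater (Table 2) | Can staff blinding protect it? |
|---|---|---|---|
| PHQ-9 | primary | client, told the arm | no |
| GAD-7 | secondary | client, told the arm | no |
| WHO-5 | secondary | client, told the arm | no |
| CSSRS | secondary | clinician | yes, in part |

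Read literally, the bar covers assessors of an outcome that has no staff rater. It does not expressly cover the CSSRS rater or the person who extracts administrative data.

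**5. Which ratings could be exposed?** Follow-up CSSRS ratings at three time points: the first visit (1 month in Table 2, 6 weeks in Data Collection and Follow-Up Assessment), 3 months and 6 months. Baseline is uncertain. Milestone 2.1 in Table 1 lists baseline assessment before randomisation, whereas Randomization and Blinding ties the code to the signing of consent. If the Table 1 order holds, the baseline rating cannot be affected.

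**The case against.** A reader might infer that the code recipient does rate the CSSRS or extract the service data, so that the workflow itself unblinds those data. The documents do not support that. Each mention of a blinded researcher is indefinite, and with four centres these may well be different people. If they are, the statements can all hold together: one person receives the codes, and others without access to them do the rating. The denial of database access is also a real safeguard, and weak wording on blinding does not contradict it. This stands, and it limits the point to what the text permits.

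A reader might also infer that all 200 allocations, and hence all CSSRS ratings, are compromised. The figure of 200 counts messages passing through the role, not biased ratings, and baseline may precede randomisation. The compiled service-use data are not among the measures under Outcome Measures or in Table 2.

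The stakes are limited too. The CSSRS is secondary, and its screening version consists of Yes/No answers from participants who know their arm, so a blinded rater gives only partial protection. A condensed article may also leave role assignments to a fuller document.

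That last argument does not remove the point. The concern is not missing detail. The article itself calls the code recipient blinded, makes assessor blinding optional, and elsewhere claims it as achieved.

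**Conclusion.** The point holds as a contradiction in the text and a gap in coverage, not as proof of unblinding. Calling the recipient of the codes blinded cannot be right for the allocations that person has read. The permissive sentence on assessors conflicts with the rater-blinded label and with the stated strength. The access bar is attached to the primary outcome, where no staff rater exists, and the CSSRS is not clearly covered.

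In extent, this touches one scale of four, a secondary outcome, at three follow-up visits, together with the 6-month administrative data. The documents allow no estimate of the bias. The claim that rater bias is eliminated is unsupported for the primary PHQ-9 however the staff roles are arranged, because unblinded participants rate it themselves.

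The verdict assumes that the texted code reveals the arm to its recipient and that the access bar means what it literally says. It should be corrected before enrolment begins; the Results section says that recruitment has not started.

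**What to change.** 1. Send each code to a designated unblinded allocation role. This person takes no part in eligibility or recruitment decisions, CSSRS rating, administrative data extraction or analysis. The separation from recruitment matters because the sequence uses permuted blocks, so someone who holds past allocations may be able to guess the next one.
2. Do not simply pass the codes to whoever carries out the step in Interventions where intervention participants "will be assisted by a study team member to register into the Text4Support program". That person must know the arm, but Recruitment Process also has a study team member approach patients. The role is suitable only if it is kept out of recruitment.
3. Make assessor blinding mandatory instead of permissive. Extend both it and the bar on the code database to CSSRS raters and to those who extract administrative data.
4. Ask participants not to reveal their arm to the CSSRS rater.
5. In the Abstract, Study Design and Setting, and Strengths of This Study, limit the rater-blinding claim to the CSSRS and state that the PHQ-9 is self-rated by unblinded participants.

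Cost: a few sentences, some reassignment of existing tasks at the sites, and a less favourable blinding claim. Whether any site needs another person cannot be judged, since the article gives no staffing numbers. Milestone 1.1 in Table 1 does assign research support, rTMS application and Text4Support delivery to one trainee, so the separation needs checking there.
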